### Outcome Measures

This study aimed to investigate the impact of HI on the 5 aspects of life-course trajectory, listed in the following sections.

#### Early Childhood Development and School Readiness

The Australian Early Development Census (AEDC) is a cross-sectional national census of all children at the time of school entry, and it has been conducted triennially since 2009 [60]. The AEDC involves classroom teachers assessing children, aged about 5 years, across 5 domains of early childhood development, associated with readiness for school learning, namely physical health and well-being, social competence, emotional maturity, language and cognitive skills (school based), and communication skills and general knowledge. The score for an AEDC domain is marked on a scale of 0 to 10, with higher scores indicating higher levels of development. A score falling below the 10th percentile of the national AEDC population indicates a *developmentally vulnerable* result on that domain [61].

Data on the outcomes of early childhood development will be accessed from the AEDC dataset, one of the linked administrative datasets used in this study. The AEDC data available for this study contain data from the censuses held in 2009, 2012, and 2015. The first type of outcome variables is directly available in the AEDC dataset and are the dichotomous results of developmental vulnerability for individual domains and the summary measure of *being developmentally vulnerable on two or more domains* (DV2). Children assessed as vulnerable on 2 or more domains are considered to be at higher developmental risk, and they generally require additional support to progress through early schooling.

The second type of outcome variables is the domain scores, which are continuous variables. These outcome measures will be used because of the fact that a high proportion of children in our study cohort have been assessed as *vulnerable*, using the dichotomous outcome variables [61], and the use of continuous domain scores is anticipated to be more sensitive in detecting differences among groups. We will use the scores for individual domains in domain-specific analysis and the sum of the scores of the 5 domains as a general indicator of children’s overall readiness for school learning.

#### School Attendance in Year 1 of Primary School

The outcome measure for this component will be children’s annual school attendance rate for Year 1 (aged approximately 6-7 years). Year 1 is chosen, as it is the first year of compulsory school attendance in the NT and as, in the study population, school attendance rates decrease with increasing year level. The data source will be the School Attendance dataset, provided by the NT Department of Education, which contains records of enrollment and daily attendance status for students studying in NT Government schools for the period 2005 to 2016. The school attendance outcome will be expressed as the number of school days attended per year, with approximately 200 school days available per year.

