**Methods:**

Individual-level information linked across multiple administrative datasets will be used to conduct a series of retrospective observational studies on selected developmental and school outcomes. The predictor variables for all studies are the results from audiometric hearing assessments. The outcome measures are as follows: Australian Early Development Census results, representing developmental readiness for school, assessed around 5 years of age; Year 1 school attendance rates; Year 3 school-based academic performance, assessed in the National Assessment Program—Literacy and Numeracy; incidence of child maltreatment events (including both notifications and substantiated cases); and incidence of a first guilty verdict for youth offenders. Confounding and moderating factors available for the analysis include both community-level factors (including school fixed effects, socioeconomic status, level of remoteness, and housing crowdedness) and individual-level factors (including maternal and perinatal health and hospital admissions in early childhood).

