### Objectives

To address this research gap, the Hearing Loss in Kids (HeLoKids) Project aims to apply a life-course epidemiological approach [45] to investigate the association between HI and developmental, educational, and social outcomes in Aboriginal children living in remote Northern Territory (NT) communities. By using linked administrative datasets containing longitudinal unit-record data for health, education, child protection, and youth justice systems, as well as hearing assessment results, this study is able to examine the selected outcomes while controlling for a wide range of potential confounders and moderators, as illustrated in the conceptual model in Figure 1.

Specifically, the study will undertake a series of studies that test the following hypotheses:

HI is independently associated with poorer developmental outcomes at the time of entry into full-time school (aged about 5 years).HI is independently associated with lower school attendance rates in Year 1 (aged about 6-7 years).HI is independently associated with poorer academic achievements in Year 3 (aged about 8 years).HI is independently associated with higher risk of child maltreatment.HI is independently associated with higher risk of youth offending.

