### Statistical Analysis Plan

For each component study, statistical analyses will start with descriptive statistics to examine the distribution of key demographic, control, predictor, and outcome variables in the study cohort. The approach of complete-case analysis will be adopted in regression analysis. As this approach may lead to exclusion of participants with missing data, we will include comparisons of the study cohort and those excluded from analysis using suitable statistical methods (z-test, *t* test or chi-square analysis) to assess the differences between the 2 groups. When the groups are found to be statistically different on any number of included variables, we will include discussion of the implications of these differences on the validity of the study’s findings.

The dependent variable, HI, is structured as an ordinal variable, and we anticipate a *dose-response* relationship between the levels of HI and the outcome variables. In all regression analyses, the investigation of associations will use *normal hearing* as the reference category.

The study investigating the impact on AEDC outcomes will use logistic regression for dichotomous outcomes and linear regression on continuous ones. In the studies investigating the impact of HI on Year 1 attendance rates and NAPLAN results, multivariate linear regression models will be fitted to estimate the association between HI and the school-based outcome measures, and the models will include school-fixed effects to control for the average observed and unobserved differences in schools and students of the schools. In the studies examining the association between HI and child maltreatment and between HI and youth offending, multivariate survival analysis will be used by fitting Cox proportional hazard models.

In these component studies, a parsimonious model building strategy will be adopted in the regression modeling process. Univariate regression analysis will first be carried out to select variables with *P* value<.25. These and all possible 2-way interaction terms will be fitted in the multivariate regression model–building process. Variables deemed to be key confounders or moderators selected on the basis of past studies will be retained throughout the model-building process.

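### The Year 1 attendance outcome is defined both as a rate and as a count of days against a fixed 200; if the count is analysed as written, time not enrolled lowers it just as absence does

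*Protocol article*

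**What the plan says.** The section on Year 1 attendance opens with the outcome as a rate: "The outcome measure for this component will be children’s annual school attendance rate for Year 1 (aged approximately 6-7 years". It closes with a count: "The school attendance outcome will be expressed as the number of school days attended per year, with approximately 200 school days available per year". Between the two it describes the source, which "contains records of enrollment and daily attendance status for students studying in NT Government schools for the period 2005 to 2016".

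Elsewhere the outcome is always a rate. The abstract has "Year 1 school attendance rates", the second hypothesis under Objectives reads "HI is independently associated with lower school attendance rates in Year 1 (aged about 6-7 years", and the Statistical Analysis Plan section says "In the studies investigating the impact of HI on Year 1 attendance rates and NAPLAN results, multivariate linear regression models will be fitted", with school fixed effects. The last paragraph of that section uses Year 1 attendance again, as a mediator between HI and youth offending in the structural equation model (SEM).

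The article does not say whether days enrolled serve as a denominator or how part-year enrolment is handled. The Study Cohort section leaves further eligibility criteria to each component study.

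**The concern.** A day count can stand in for a rate only when the number of days at risk is the same for everyone. Here the source covers government schools in one territory. A child who enrols late, leaves the territory or moves to another school sector has fewer recordable days, and attendance elsewhere is not seen. Against a fixed 200 days, those unseen days are indistinguishable from days absent.

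At stake is what hypothesis 2 tests. With the count, the coefficient for HI mixes attendance while enrolled with length of enrolment. Variation in enrolment length adds variance, and an association between HI and enrolment length would appear as an attendance effect of either sign. The SEM would take the same mixture into its indirect pathway.

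**Working it through.** There is no sample size, power or effect figure for this component to reproduce. The check is therefore arithmetic on the definition.

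**Inputs from the article:** about 200 school days per year; outcome called a rate in some places and a count of days in one; source limited to NT Government schools; enrolment and daily attendance records held.

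**Inputs assumed, because the article gives none:** attendance while enrolled, *p*, of 60% or 80%; enrolled days *e*; the share *f* of children enrolled for half the year (100 days).

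**Step 1. One child.** Count = *p* × *e*. Rate scaled to a full year = (days attended ÷ *e*) × 200 = *p* × 200.

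| *p* | *e* | Count | Count ÷ 200 | Rate × 200 |
|---|---|---|---|---|
| 80% | 200 | 160 | 80% | 160 |
| 80% | 150 | 120 | 60% | 160 |
| 80% | 100 | 80 | 40% | 160 |
| 80% | 50 | 40 | 20% | 160 |
| 60% | 200 | 120 | 60% | 120 |
| 60% | 100 | 60 | 30% | 120 |

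A child enrolled for 100 days at 80% and a child enrolled for 200 days at 40% both score 80 on the count.

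**Step 2. Two groups with the same true attendance.** Mean count = *p* × 200 × (1 − *f*) + *p* × 100 × *f*. The false difference is therefore −100 × *p* × (*f*₁ − *f*₀), where *f*₀ is the share in the normal-hearing group and *f*₁ the share in an HI group. For *p* = 60%, *f*₀ = 10% and *f*₁ = 20%: 200 × 0.6 × 0.95 = 114 and 200 × 0.6 × 0.90 = 108, a difference of −6 days.

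| *f*₀ | *f*₁ | *p* = 60% | *p* = 80% |
|---|---|---|---|
| 10% | 10% | 0 | 0 |
| 10% | 15% | −3 | −4 |
| 10% | 20% | −6 | −8 |
| 10% | 30% | −12 | −16 |

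If part-year enrolment were commoner among children with normal hearing, the signs would reverse. With the rate, or the rate × 200, every entry is 0.

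**Step 3. Noise when shares are equal.** In a simulation with individual rates drawn around 60% (SD 20 percentage points, truncated at 0 and 100%), the SD of the full-year value was 39.1 days. With 10%, 20% and 30% of children enrolled for half the year, the SD of the count was 41.6, 43.2 and 44.0 days. The variance ratios are (41.6 ÷ 39.1)² = 1.13, (43.2 ÷ 39.1)² = 1.22 and (44.0 ÷ 39.1)² = 1.27. The simulation treats each child's rate as known exactly, so it leaves out the extra imprecision of a rate measured over a short enrolment.

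**Step 4. Do the planned models remove the effect?** School fixed effects absorb differences in average enrolment length between schools. They do not absorb differences between children in the same school. The Control Variables section does not name enrolment length, although it leaves the selection open for each component.

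**The case against.** The strongest reply is that the last sentence of the outcome section only gives a reporting unit. The outcome is introduced as a rate, and every mention outside that section uses the same term. The source is said to hold enrolment records, which a proper rate needs. On that reading 200 is a conversion factor and the bias in Steps 1 and 2 disappears. This reading is plausible and the text does not exclude it. Nor does the text state it, and the sentence as printed gives a count.

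A reader might infer that the plan does score non-enrolled days as absence, and so that the attendance result will be biased. The article does not support that. It nowhere says how such days are treated. Even with the raw count, the HI contrast is biased only if enrolment length differs by HI level within schools after adjustment. The article gives no evidence of such a link and no share of children enrolled for part of the year.

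A reader might also fault the article for lacking a minimum enrolment period, or for choosing linear regression over a fractional or binomial model. Neither stands as an error. An enrolment threshold is detail that a condensed article may leave to the full plan, and the Study Cohort section leaves room for it. The choice of model family is a preference that the denominator question does not settle.

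What remains is more than missing detail: the article states a derivation, and read literally it conflicts with the outcome it names.

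**Conclusion.** The point holds as an inconsistent outcome definition with a conditional consequence. The conflict between rate and count is certain, since both stand in one section. That the count depends on enrolment length is also certain if the count is what is analysed.

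The effect on the HI estimate is not known. The 3 to 12 days at 60% attendance, and 4 to 16 days at 80%, rest entirely on assumed shares of half-year enrolment. They illustrate scale and are not estimates for this cohort. If the shares are equal across HI groups with equal attendance, the false difference is 0 and the main cost is added variance. If the analysed variable is an enrolment-based rate, neither effect arises, and the correction is one of wording.

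**What to change.** State one analysed outcome: days attended divided by days enrolled during Year 1, both taken from the government school records and summed over all government schools the child attended in that year. Use days per 200 only to present results. Use the same variable for Year 1 attendance in the SEM.

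Two optional checks would show whether short enrolments matter: weighting the linear regression by enrolled days, or repeating it in children enrolled for most of the year.

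The cost is one extra derived variable from data already held. The drawback is that rates for children with short enrolment are less precise, which is what the optional checks address.

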#### Academic Performance in Year 3 of Primary School

The outcome measure for children’s academic performance in early years of primary school will be taken from the National Assessment Program–Literacy and Numeracy (NAPLAN) dataset. NAPLAN is an annual national assessment program, which commenced in 2008, and is undertaken by all students in Australia in years 3, 5, 7, and 9 (aged approximately 8, 10, 12, and 14 years, respectively) [62]. NAPLAN includes separate tests for numeracy, reading, writing, and language conventions (which include spelling, grammar, and punctuation). The test contents are developed to include specific considerations for Indigenous education, English as a second language, and special needs education [63]. The tests are designed to assess students’ understanding of the core elements of the national curriculum and to assist schools and teachers to identify students who may not have learned the skills required to progress academically. The raw score for each test is converted into a scaled score out of 1000. Data were available from 2008 to 2016. The outcome measures for this study will be the scale scores for the 5 NAPLAN domains for Year 3. The selection of Year 3 optimizes the study cohort by avoiding both the declining school attendance and declining participation in NAPLAN assessments in later years.

#### Child Maltreatment

The data source for this study is the NT Government Child Protection dataset, which is a statutory data collection of child maltreatment—related contacts with child protection services. The research dataset will include information on all notifications (reports), substantiated cases, and episodes of out-of-home care. The outcome measures for this study will be the cumulative incidence of first notification of child maltreatment and the cumulative incidence of first substantiated case of child maltreatment. The time to event will be calculated from date of birth to the earliest of the following: date of each event of interest, date of death, the last observed date in the linked datasets, or the designated end of follow-up date for the study. Data are available from 1999 to 2017.

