### Remote Hearing Assessment Dataset

The Remote Hearing Assessment (RHA) dataset contains middle ear examination and audiometric assessment information collected by the NT Outreach Hearing Health Program [58]. This program is an Australian Government funded specialist ear and hearing health outreach service, available to all NT Aboriginal children and young people, aged under 21 years, most of whom live in remote communities.

The NT Outreach Hearing Health Program uses pure tone audiometry to assess children’s hearing ability and determine the type (sensorineural, conductive, mixed, or indeterminate) and level of hearing loss. The level of hearing loss of an ear is calculated by taking the average of the thresholds of hearing (as deviation from normal threshold, in decibels Hearing Level—dB HL) for 3 frequencies: 500 Hz, 1000 Hz, and 2000 Hz. The results for each ear are classified as either normal or 1 of 4 ordinal categories of hearing loss, namely mild (16-30 dB HL), moderate (31-60 dB HL), severe (61-90 dB HL), and profound (91 dB HL or greater). This relatively conservative classification of hearing loss was chosen over the more widely used World Health Organization classification, as it is deemed more suitable for children aged under 15 years [58,59]. Further details on this classification of hearing loss are available elsewhere [58]. The clinical assessment for each ear is also recorded and classified under the following categories: acute OM (AOM), AOM with perforation, CSOM, dry perforation, Eustachian tube dysfunction, increase in middle ear pressure, OME, normal, and others.

The dataset provided to this study includes information collected from 2007 to 2015, for over 8000 children and young people aged between 0 and 21 years, which is about 22% of the NT Aboriginal population in this age group. Children and young people access these services through referral by primary care services. From January 2013, access to these services was prioritized according to clients’ need for service. This means that the children and young people whose records are captured in the RHA dataset are not a random sample of the general population, and the information is likely to be biased toward those with abnormal middle ear examination and hearing difficulties.

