### The Study Cohort

The study cohort comprises NT-born Aboriginal children, with hearing assessment results in the RHA dataset and with a residential location classified as *remote* or *very remote* on the basis of ARIA+ [48]. Further inclusion and exclusion criteria will vary among the component studies of this study, depending on the respective requirements. In principle, as the data analysis will be based on a complete-case analysis, only children with data in the selected dependent, outcome, and control variables will be included. Children who have had surgical treatment for OM before the age of 4 years will be excluded, as the surgery could alter the impact of HI during the early childhood period. This will be done by searching in another linked administrative dataset, the NT Hospital Separations Dataset, and excluding children admitted before the age of 4 years, with any diagnosis code plus any procedure code related to OM and its treatment (Table 1).

**Table 1 table1:** Otitis media—related hospital admission diagnoses and surgical procedures used to exclude children who had received surgical treatment, with International Classification, 10th Revision-Australian Modification codes.

ICD-10AM^a^ Code		Diagnosis/procedure

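### Maltreatment follow-up starts at birth, but child protection records start in 1999 and the cohort rule admits earlier births, so unobservable early years count as event-free

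*Protocol article*

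**What the plan says.** The Child Maltreatment section names two outcomes, the "cumulative incidence of first notification of child maltreatment and the cumulative incidence of first substantiated case of child maltreatment". Both are first events. The time origin is birth: "The time to event will be calculated from date of birth to the earliest of the following". The list that follows contains only ways to leave follow-up: the event, death, the last observed date, or the end of the study period. No entry rule is given. The section closes with the data window: "Data are available from 1999 to 2017".

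The Remote Hearing Assessment (RHA) Dataset section says that the hearing file "includes information collected from 2007 to 2015, for over 8000 children and young people aged between 0 and 21 years". The service itself is "available to all NT Aboriginal children and young people, aged under 21 years".

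The Study Cohort section sets the general rule: "The study cohort comprises NT-born Aboriginal children, with hearing assessment results in the RHA dataset", with a remote or very remote residence. It gives no birth-year limit and adds: "Further inclusion and exclusion criteria will vary among the component studies of this study, depending on the respective requirements". No further criterion is stated for maltreatment. The Dependent Variables section accepts the first hearing test at whatever age it took place. The Statistical Analysis Plan section names Cox proportional hazards models and mentions no delayed entry.

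**The concern.** A first event timed from birth can be observed only if the records cover the child's whole life. For a child born before 1999 they do not. Two errors follow if the stated rules are applied:

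- The years from birth to the start of 1999 enter the risk sets, although no event could have been recorded in them.
- A child who had a contact before 1999 and another afterwards is recorded as having a first event at the later age. A child whose only contact came before 1999 is recorded as never having had one.

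Cumulative incidence is the stated outcome measure, so it is hit directly. The hazard ratio for hearing impairment (HI) is at risk as well. The affected children are the older ones, and they were necessarily tested at older ages. If measured hearing differs by age at test, the missing events are spread unevenly over the HI groups.

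**Working it through.** The article gives no sample size, event count or birth-year distribution, so there is no figure of its own to reproduce. The check uses its dates, then assumed distributions to show a range.

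**1. Which births are allowed.** Inputs are the hearing test years (2007 to 2015) and upper age (21), from the RHA Dataset section. Earliest birth year = first test year − maximum age = 2007 − 21 = 1986, or 1985 if a completed age of 21 is included. If the oldest clients were seen only in the last year, it is 2015 − 21 = 1994. Every reading reaches back before 1999.

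**2. Unobservable years.** Years lost = 1999 − birth year, as a share of ages 0 to 18:

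| Birth year | Years lost | Share of 0–18 |
|---|---|---|
| 1986 | 13 | 72% |
| 1990 | 9 | 50% |
| 1994 | 5 | 28% |
| 1998 | 1 | 6% |

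**3. Age at test.** A child born before 1999 was older than 2007 − 1999 = 8 at a 2007 test and older than 2015 − 1999 = 16 at a 2015 test. All affected children were therefore at least 8 when tested.

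**4. Cumulative incidence.** The recorded first contact can never precede the true first contact, so the recorded curve for these children cannot lie above the true one. As an illustration, assume contacts at a constant rate *h* per year, with the first contact after 1999 taken as the first. True incidence by age 18 is 1 − exp(−18*h*); recorded incidence is 1 − exp(−*h*(18 − years lost)).

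| Assumed *h* | True | Recorded, 1986 births | Recorded, 1994 births |
|---|---|---|---|
| 0.02 | 30% | 1 − exp(−0.02×5) = 10% | 1 − exp(−0.02×13) = 23% |
| 0.05 | 59% | 1 − exp(−0.05×5) = 22% | 1 − exp(−0.05×13) = 48% |

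**5. Share of the cohort affected.** This is not in the article. With test dates uniform over 2007 to 2015, the assumed share born before 1999 is about 40% if age at first test is uniform over 0 to 21, 12% if its mean is 7 years, and 4% if its mean is 5.25 years (beta-shaped ages for the last two).

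**6. Hazard ratio under a true null.** Simulations set the true HI hazard ratio to 1, the hazard to 0.03 to 0.10 per year, and the share with normal hearing to rise from 25–30% at age 3 to 50–65% at age 18. That gradient is an assumption.

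| Birth or test-age mix | Born before 1999 | HR, clock from birth |
|---|---|---|
| Test age mean 5.25 (gamma) | about 6% | 1.00–1.03 |
| Test age mean 7 (gamma) | about 13% | 1.03–1.08 |
| Test age mean 9 (gamma) | about 21% | 1.04–1.11 |
| Births uniform 1986–2012 | 13/27 = 48% | roughly 1.1–1.3 |

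In the last row, builds that differed in detail gave 1.06–1.16, 1.08–1.26 and 1.13–1.34. Restricting to births from 1999 returned 1.00–1.02 in one build and 0.95–1.01 in another; the latter used single runs with Monte Carlo error of about 0.02 to 0.03.

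**7. Offending component.** Its clock starts at the 10th birthday and its data in 1997. A 10th birthday before 1997 means birth before 1987, so only the oldest one or two birth years fall outside the window.

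**The case against.** The strongest reply is that the article expressly leaves component-specific criteria open, and a birth-year limit set by the outcome data is just such a criterion. The article writes out no birth-year range for the school components either, though their data windows imply one. A birth origin is perfectly valid for children born from 1999. An unstated restriction could therefore already remove the problem. This stands as a reason for restraint about severity. It does not remove the point: the Child Maltreatment section sets origin, exits and data window in one paragraph, and with the stated cohort rule they do not fit together.

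A reader might also infer more than the documents support:

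- *That the cohort contains births back to 1986.* That year is an outer bound implied by dates and ages, not a printed fact.
- *That 13 of 30 birth years (1986 to 1998 out of 1986 to 2015) measures the damage.* It counts calendar years, not children. The affected share could be about 4% or about 40%.
- *That the plan will produce a false positive HI association.* This needs hearing to be better at older first-test ages, which the article nowhere says. It describes access by referral, prioritised by need from 2013, so older children tested could be better or worse. A reversed gradient would reverse the sign.

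Cox regression does not rescue the rule, since right censoring deals with exit and not with unobserved time at entry. Adjusting or stratifying for birth year could lessen the hazard ratio bias, but the Control Variables section does not name birth year, and no adjustment recovers missing first events.

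**Conclusion.** The point holds. As written, the time origin, the data window and the cohort rule together count unobservable time as event-free for any child born before 1999 and can mislabel later contacts as first. Downward bias in cumulative incidence for those children follows from the definitions alone; its effect on the whole cohort depends on how many there are. Bias in the HI hazard ratio is possible but not established. It is negligible if few children were born before 1999, and reaches hazard ratios of roughly 1.1 to 1.3 under a true null if about half were and hearing improves with age at test. Both conditions are assumptions, and the direction cannot be set from the documents. The offending component is barely touched, and it would be wrong to read the same defect into it on any scale.

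**What to change.** State for the maltreatment component that the primary analysis includes only children born on or after the start of complete child protection records (1999), so that first notification and first substantiation are observable from birth. Adjust or stratify for birth year. If older births are to be shown at all, report them in a sensitivity analysis with entry to the risk set delayed to 1999. On that basis a 1986 birth enters at about age 13 and contributes about 5 of 18 childhood years. Delayed entry should not be the primary analysis, because it leaves unknown whether a recorded event is truly the first. Report how many children were born before 1999. For offending, check that the 10th birthday falls within the data window (births from 1987); nothing more is needed.

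The change is one inclusion criterion and needs no new data. The cost is the loss of the older birth cohorts, and their later-childhood follow-up, from this component. The number lost cannot be computed from the article, but the study team can count it from the linked file.
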